### Sample size

Assuming that 30% of patients in the polyurethane arm will show healing of PrU-II at 8 weeks, an alpha risk of 5%, a beta risk of 20% with bilateral contrast and a loss to follow-up of 15%, 410 individuals will be required in each treatment arm to detect a ≥10% difference in healed ulcers [22,23].

### Blinding

Due to an inability to mask the appearance of the two dressings, it will only be possible to mask the final evaluation of PrU.

### Interventions

Participants will be randomized to hydrocolloid or polyurethane dressing. All patients will receive a standardized preventive intervention to reduce pressure and undergo a PrU healing cure process.

**
*Transversal interventions*
** are designed for pressure relief and positional changes, favoring an optimal evolution of stage II PrU (PrU-II). Adequate relief of pressure forces (shearing or friction) requires changes in position of bedridden or sitting patients and the use of pressure-relieving support surfaces (PRSS).

Due to their structure, PRSS can reduce pressure forces, as well as heat and humidity, increasing patient comfort. PRSS can cover the entire body or only part of it and can be found in different sizes and types: mattresses, mats or cushions. However, it is important to highlight that the use of PRSS does not mean ignoring other healing procedures, including changes of position, skin care and good nutritional state. Rather, PRSS use only serves as a complement to the healing process [1].

To standardize changes in position and pressure reduction, study nurses will follow a national GCP recommendations [1]. Recommendations for frequency of position changes, as well as specific recommendations for bedridden and sitting patients, must be taken into account. Each study nurse or caregiver will be trained to properly implement the recommendations in the aforementioned GCP.

**
*Healing cure process*
** addresses the cleansing process and prevention of infection. Standardization of this process can be accomplished using recommendations from the reference GCP. Briefly:

*The wound must be cleaned every time the study dressing is changed*. The first step is to thoroughly irrigate the wound bed with saline solution to remove detritus, bacteria and remains of any previous treatment. A 20 ml syringe of saline solution adapted with a 0.9 × 25 needle or a 19 mm catheter. Local antiseptics (e.g. povidone, chlorhexidine) and skin cleaners should be avoided because they are cytotoxic to new granulating tissue and their habitual use can have systemic effects due to absorption.

*The drying procedure must be also delicate*. Rough material (such as gauzes or sponges) can induce small traumas on the wound bed, increasing the risk of infection and interfering with the healing process. Wound edges should be dry and clean and wound beds moist. Care should be taken to avoid damaging healthy tissue during cleansing and drying procedures.

*Bacterial infection should be prevented*. An aseptic technique should be used if possible, including the use of clean gloves. Proper healing and debridement procedures can minimize the risk of infection. If a patient presents with more than one PrU-II, the most contaminated one should be left to the end (i.e. perennial area).

It is important to isolate and remove waste and contaminated materials in accordance with established precautions to avoid cross contaminations.

If there is leakage of exudates, lack of adherence or any situation suggesting loss of study dressing, additional (secondary) dressings will be used. If this additional support is inadequate, the study dressing will be changed following the same procedure and be registered in the CRF.

### Study dressings

#### Polyurethane foams

##### Description and features

These dressings derive from polyurethanes and have a hydrophilic structure. They present with a high capacity of autolytic debridement and absorption of exudates; and keep the wound bed from drying out, without leaving residuals or decomposing. In addition, they avoid leakages, stains and odors, keep periwound skin intact, reduce frictional forces and do not produce traumas when removed.

##### Indications

These dressings are recommended for all stages of PrU (with moderate or high exudates). Frequent monitoring and changes may be necessary when PrUs become infected.

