## Background

Pressure ulcers (PrUs) are ischemic wounds in the skin and underlying tissues, caused by continuous pressure from friction or shearing between an external surface and a bone or cartilaginous surface. Long-standing pressure can reduce capillary blood flow and lead to cell death, necrosis and broken tissue, or to additional serious complications, including osteomyelitis, sepsis, contractures, atrophy and psychological disorders [1,2]. These complications may delay mobilization and active rehabilitation, as well as reducing the ability of patients to live active and independent lives. PrUs can affect patients in all health care settings, provoke pain and discomfort, decrease quality of life and even increase morbidity and residence time in healthcare institutions [3,4].

PrUs can also increase direct and indirect healthcare costs and provide a negative image of healthcare institutions, attributable to deficits in the quality of care, especially since 95% of PrUs are preventable [1,2]. A national study has estimated that expenditures related to the onset of PrU amounts to approximately 5% of the annual healthcare spending in Spain [3,4].

A national prevalence study in 2006 by the GNEAUPP (Spanish acronym of National Group for the Study and Advice in Pressure Ulcers and Chronic Wounds) showed a wide variability in PrUs prevalence among types of institutions. PrUs have been reported to occur in 3.73% of patients in domiciliary care, 8.24% of hospitalized patients and 6.1% of patients in nursing homes. Moreover, 2.1% of patients with PrUs were aged 0 to 45 years, 6.4% were aged 46 to 64 years and 87.4% were aged ≥ 65 years [5]. Within each category, PrU incidence was very variable, ranging from 3-29% in hospitalized patients. Moreover, PrUs have been observed in 66% of elderly individuals (risk population) with femur fractures [4-7].

The European Pressure Ulcer Advisory Panel (EPUAP) has classified PrUs in four stages. Stages I and II are more frequent, with a combined rate of about 65% [5], although it differs among studies [8-15]. The EPUAP has defined stage II PrU (PrU-II) as involving a partial loss in skin thickness, affecting the epidermis and/or dermis. These are considered superficial ulcers, clinically manifesting as abrasions or blisters [8,16].

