#### Inclusion criteria

Age ≥ 18 years.

Confirmed diagnosis of PrU-II. If a patient has more than one PrU-II, only the largest diameter ulcer will be assessed. Other PrU-II will receive the best treatment elected by the study nurse.

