#### Exclusion criteria

Stage I, III or IV PrU only.

Non classifiable PrU.

Surgical treatment prior to PrU and/or PrU in previously irradiated areas.

Participation in another clinical trial within 3 months of study entry.

Allergy or hypersensitivity to materials in the study dressings.

Signs of PrU basal infection (sepsis/bacterial), cellulitis or osteomyelitis. Patients successfully treated for infection can be included if the PrU can be classified as stage II.

Venous ulcers and/or diabetic feet.

Type I diabetes.

Situations of extreme severity and/or agony; e.g. patients in terminal phase with <3 points on the Braden scale and/or a life expectancy < 1 month.

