##### Indications

These dressings are recommended in non-infected PrU stages I, II and III; slough ulcers and those with necrotic tissue (as an autolytic debriding agent) and granulation phase or epithelialization healing process.

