##### Contraindications

These dressings should not be applied to infected ulcers or those in which bones or tendons are observed. Ether and aggressive antiseptics should be avoided when using these dressings [1,3].

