### Work plan

Before the trial begins, the study protocol will be presented to all research team members in a special meeting. A training session lasting 3–4 h will include a review of the inclusion and exclusion criteria, provide instructions regarding interventions and the procedure to use to fill out the Case Report Form (CRD), as well as assessing the ethical requirements for the trial. The protocol to be used to collect information from each patient at each study visit will include (see Additional file 2: Table S1):

•**Selection visit (screening)**

Assessment of inclusion/exclusion criteria

Signing informed consent form

•**Visit 1 (baseline).***If patients agree to participate in the study at the selection visit, all scheduled activities for visit 1 can be performed at the selection visit. If patients require time to think about participating, these scheduled activities will be performed at visit 1.*

Randomization process

Collection of demographic data, including date of birth, sex, and place of usual care

Risk factors for PrU, using the Braden scale

PUSH Scale registry, including area of each lesion (width × length), volume of exudates and tissue type

PrU photographic registry

Healing process registry: reason to change dressing, time treated by the nurse, materials used

Training about transverse care (positional changing and pressure reduction)

Recording of concomitant medications

Recording of adverse events

•**From Visit 2 to Visit 7 (Follow-up)**

Assessment of inclusion/exclusion criteria

Assessment of transverse interventions, from each patient’s diary and nursing files

PUSH Scale registry, including area of each lesion (width × length), volume of exudates and tissue type

Healing process registry: reason to change dressing, time treated by the nurse, materials used

Recording of concomitant medications

Recording of adverse events

•**Between visits.***The study protocol includes 8 study visits. If patients require a change of dressing, between visits,it must be recorded in the CRF, with the following information collected.*

Date of dressing change

Reason for dressing change (exudates, lack of adherence, other reasons)

Time treated by the nurse (mm:ss)

Materials used

•**Visit 8 or End of study**

PUSH Scale registry: diameter of each lesion (width × length), volume of exudates and tissue type.

Completion of the dressing scale comfort instrument by patients and study nurses

Braden scale

PrU photographic registry

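### The protocol's stated indication for foam is limited to moderate or high exudate but eligibility is not, so low-exudate ulcers fall outside the stated indication in the foam arm only; the effect on the comparison is unknown in size and direction.

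*Protocol article*

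**What the plan says.** All references are to the protocol article.

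- **Study dressings, Polyurethane foams, Indications:** "These dressings are recommended for all stages of PrU (with moderate or high exudates"). The exudate qualifier stands in brackets after the reference to all stages.
- **Study dressings, Hydrocolloids, Indications:** "These dressings are recommended in non-infected PrU stages I, II and III; slough ulcers and those with necrotic tissue". No exudate level is named.
- **Study dressings, Hydrocolloids, Contraindications:** "These dressings should not be applied to infected ulcers or those in which bones or tendons are observed".
- **Inclusion criteria:** "Confirmed diagnosis of PrU-II", with no exudate condition.
- **Exclusion criteria:** these include "Signs of PrU basal infection (sepsis/bacterial), cellulitis or osteomyelitis". None of them mentions exudate.
- **Background:** of stage II ulcers, "These are considered superficial ulcers, clinically manifesting as abrasions or blisters". Their exudate level is not described.
- **Work plan, Visit 1:** the baseline record includes "PUSH Scale registry, including area of each lesion (width × length), volume of exudates and tissue type". It is listed after the randomization step.
- **Comparative analysis:** healing is compared by a chi-square test. A logistic model adjusted for potential confounders is added only when patients are unequally distributed between the arms.

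**The concern.** Entry to the trial matches the stated limits of one dressing but not those of the other. The hydrocolloid text restricts that product to non-infected ulcers, and infection is an exclusion criterion. The exudate qualifier on foam has no counterpart in eligibility, and the protocol does not explain the difference.

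The hypothesis concerns stage II ulcers in general. If the two dressings compare differently in low-exudate and in moderate- or high-exudate ulcers, the pooled healed percentage averages over both groups. It cannot then show how foam performs within the indication that the protocol itself gives. The stated analysis would not reveal this. Randomization should balance exudate on average, so the trigger for adjustment may never be met. Even if it were, adding exudate as a covariate would not show whether the treatment effect varies with it.

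**Working it through.** **1. The passages side by side**

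| Ulcer at entry | Eligible? | Within the stated foam indication? | Within the stated hydrocolloid indication? |
|---|---|---|---|
| Stage II, not infected, moderate or high exudate | Yes | Yes | Yes |
| Stage II, not infected, no or light exudate | Yes | No, if the bracketed qualifier is read as a limit | Yes |
| Stage II, infected | No | Not decided here | No |

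The second row is the mismatch. It exists in the foam arm only.

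**2. The plan's own sample size**

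Inputs from Sample size: 30% healing on foam, a 10-point difference (30% v 40%), two-sided alpha 5%, power 80%, loss 15%.

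- Pooled-variance formula for two proportions without continuity correction: 356 per arm.
- Loss added as 356 × 1.15 = 409.4, rounded up to 410, which is the stated figure. Dividing by 0.85 instead gives 419.
- Evaluable after 15% loss: 410 × 0.85 = 348 per arm, with 79.1% power for 30% v 40%.

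The stated figure is reproduced, and nothing in this point changes it.

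**3. What the mismatch could do to the overall difference**

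The documents give neither of the two quantities needed, so both are assumptions:

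- f = share of enrolled ulcers with no or light exudate
- d = percentage points by which foam heals these ulcers less often than hydrocolloid (negative if foam does better)

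Assume also that the dressings do not differ in moderate or high exudate, that 30% heal on hydrocolloid, and that 348 per arm are evaluable. Then:

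Overall difference (hydrocolloid − foam) = f × d

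| f | d (points) | f × d (points) | Chance of a significant result in the direction of the difference |
|---|---|---|---|
| any | 0 | 0 | 2.5% in either direction |
| 30% | 5 | 1.5 | about 6% |
| 30% | 10 | 3 | about 14% |
| 50% | 10 | 5 | about 31% |
| 50% | 20 | 10 | about 86% |
| 30% | −10 | −3 (favours foam) | about 13% |
| 50% | −10 | −5 (favours foam) | about 29% |

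The 10-point row needs half the patients to be in the low-exudate group, with 10% healed on foam against 30% on hydrocolloid. No passage supports a deficit of that size.

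**4. Precision of a result by exudate group**

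If half of the 348 evaluable per arm are in each group, each group has 174 per arm.

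- 95% half-width for the healed difference at 30% v 40%: overall 1.96 × √((0.21 + 0.24)/348) = 7.0 points; within one group 1.96 × √(0.45/174) = 10.0 points.
- Half-width for the difference between the two group effects: 10.0 × √2 = 14.1 points.
- Power for 30% v 40% within one group of 174 per arm: about 50%. Even with no loss (410 × 0.5 = 205 per arm) it is about 56%.

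**The case against.** The case on the other side is substantial.

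- **A recommendation is not a prohibition.** The exudate wording stands in a general product description. The foam contraindications list antiseptics and similar agents, not low exudate. The Background calls both dressings recommended and part of usual practice for stage II ulcers. If usual practice includes low-exudate ulcers, they belong to the question asked. This stands, and it is why the point is a request to reconcile the text and not a claim that patients are wrongly enrolled.
- **The direction is not documented.** A reader might infer that the comparison tilts towards hydrocolloid, because only foam is used outside its stated indication. The documents do not support that. No passage says foam heals low-exudate ulcers worse, and the foam description says it prevents the wound bed from drying out. This stands in full.
- **The share is not documented.** A description of superficial abrasions or blisters gives no exudate level. This also stands: how much of the foam arm is affected cannot be stated.
- **There is no confounding.** Randomization should balance exudate on average, so the overall result is a valid average effect in the enrolled population. This stands.
- **Interactions and subgroups belong in a statistical analysis plan.** In general they do, and their absence alone would be no finding. But the article does fix the method: a chi-square test, with adjustment only on imbalance. It also prints the indication and the eligibility criteria, which do not agree. Those are statements in the text, not omissions.

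**Conclusion.** The point holds in a limited form. The foam indication is narrower than eligibility, the hydrocolloid indication carries no exudate limit, and any low-exudate ulcer allocated to foam is outside the indication the protocol states. That follows from the text alone, provided the bracketed qualifier is read as a limit.

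The consequence for the comparison cannot be sized from the documents. Over assumed shares of 10% to 70% and deficits of 0 to 20 points, the overall shift runs from 0 to 14 points (0.7 × 20) against a 10-point target, and its sign reverses if foam does better in these ulcers. These figures show only how the result would depend on the two unknowns; they are not an estimate of bias. The issue is effect modification and to whom the result applies. The stated sample size is unaffected.

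A reader might also infer that the conclusion about foam should rest on the moderate- or high-exudate ulcers alone. That would be a poor exchange: at a 50% share, power for the design difference falls from about 79% to about 50%.

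**What to change.** 1. **Reconcile the text.** The inclusion and exclusion criteria and the foam indication should agree on whether stage II ulcers with no or light exudate are meant to be in the trial. Which rule is right is for the sponsor.
2. **Fix the adjustment in advance.** In Comparative analysis, replace adjustment triggered by imbalance with a healing model that always includes baseline PUSH exudate (none or light v moderate or heavy). Score it before the allocation is known. The Work plan lists randomization ahead of the PUSH record at Visit 1, and the nurses cannot be blinded to the dressing.
3. **Pre-specify a secondary estimate.** Add a treatment-by-exudate interaction, with the healed difference and its 95% confidence interval in each exudate group.
4. **Keep the primary conclusion** on the full intention-to-treat population.

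**Cost.** Items 2 to 4 need wording and a fixed order of steps at Visit 1, with no new data and no change to 410 per arm. Item 1 costs only wording if the indication text is what changes; if eligibility changes, recruitment and the population under study change too. The interaction and group estimates will be imprecise (half-widths of about 14 and 10 points at an even split) and should be read as supportive.

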##### Contraindications

These dressing cannot be combined with antiseptics (e.g. iodine, chlorhexidine, hypochlorite, ether or hydrogen peroxide), oxygenated water or sodium hypochlorite because all of the latter can destroy the dressing [1,3].

#### Hydrocolloids

##### Description and features

These dressings are made of carboxymethylcellulose (CMC) and other hydrocolloids (elastomers), adherent substances or hydroactive compounds, providing absorption capacity. They are covered with a polyurethane layer, giving them occlusive or semi occlusive properties. In addition, they absorb exudates and necrotic residuals by forming a gel with special color and odor characteristics, creating a slightly acid environment with bacteriostatic properties. Moreover, they reduce friction forces.

##### Indications

These dressings are recommended in non-infected PrU stages I, II and III; slough ulcers and those with necrotic tissue (as an autolytic debriding agent) and granulation phase or epithelialization healing process.

##### Contraindications

These dressings should not be applied to infected ulcers or those in which bones or tendons are observed. Ether and aggressive antiseptics should be avoided when using these dressings [1,3].

### Variables

#### Main outcome variables

The main efficacy outcome of the study is rate of PrU-II healing or ulcer epithelialization tissue (scored on the PUSH scales as 0). Two digital photographs will be taken, one at the beginning and the other at the end of treatment, and sent to the expert panel committee from Balearic Islands (GAUPP) for evaluation. This committee will be blinded to treatments of individual patients.

### Secondary outcome variables

#### Efficacy

*Changes in the basal PUSH scale,*[24-27] ulcer area (in cm [2]) at the end of treatment, exudates and tissue type. This information will be collected weekly until the end of the study or until the PrU-II heals.

*Changes in ulcer area in cm*[2] will be measured using ImageJ software [28,29]. Two photographs, taken at the beginning and end of treatment (8 weeks or when the wound heals), will be evaluated by members of the expert panel committee. A <10% difference in ulcer area measured by two evaluators will be considered ‘agreement’ and the final measure will be the average of these measurements. A ≥10% difference in ulcer area between the two evaluators will be considered ‘disagreement’, requiring measurement by a third investigator, with the final measure being the average of the two closest measurements. This method has been used in other studies to evaluate changes in ulcer area [30].

Cost-effectiveness (partial cost-effectiveness evaluation): cost per proportion of healed ulcers and cost per treated patient. In both treatment arms, the healing process registry must reflect information regarding dressings and material used, including cost per unit dressing, cost per secondary dressing, additional material used for each patient (e.g. saline, gauzes, globes, tubing, syringes), and time spent by each nurse performing these procedures (mm:ss).

Dressing convenience (patient comfort) [31-33] will be evaluated by both patients and study nurses using Likert scales ranging from 1 (worst outcome) to 5 (best outcome) to assess the following measures:

*Patients:* adherence to dressing; pain at dressing removal; pain during application of dressing; overall comfort; and time during the healing process

*Study nurses:* adherence to dressing; ease of applying the dressing; ease of removing the dressing; absorption by the dressing; perilesional skin condition, as assessed by erythema; perilesional skin condition, as assessed by maceration; and time during the healing process.

### Withdrawal criteria

Patients will be removed from the trial if any of the following conditions are met:

•Infection and/or progression of PrU-II

•Disease progression, requiring discontinuation of the investigational product treatment regimen or study requirements.

•An adverse event (AE) that requires discontinuation of the investigational product or study procedures.

•Voluntary withdrawal

•Loss of follow-up

Protocol deviations will be registered. In case of a serious protocol deviation, the research team will assess the possibility of withdrawing the patient from the study.

Study discontinuations must be registered in the CRF, and, where possible, tests and procedures usually performed at the final visit (visit 8 or end of study) should be carried out. Patients who withdraw due to AEs must be followed until the end of the study (8 weeks), and if necessary until AE resolution.

